### Anthropometry and body composition

Body mass will be recorded to the nearest 0.1 kg using a calibrated digital scale (AND Weighing; HW-KGL, Melbourne, Australia) with participants wearing light figure hugging clothing and without footwear. Height will be measured to the nearest 0.1 cm whilst barefoot using a wall-mounted stadiometer (Holtain Limited, Crymych, United Kingdom), with the participant’s head positioned in the Frankfort plane. BMI will be calculated as weight (kg) divided by the square of height (m^2^).

Whole-body and regional body composition will be estimated using Dual-energy X-ray absorptiometry (DXA) (Lunar iDXA; GE Healthcare, Madison, WI) with analysis performed using the GE enCORE bone densitometry software (version 16; GE Healthcare). The system software provides estimates of FFM, lean soft tissue, FM and bone mineral density (BMD) for total body and body segments including both arms, both legs and the trunk. ASM was calculated as the sum of lean soft tissue mass in both arms and legs [55], with the ASM index calculated using the formula, ASM/height^2^ (kg/m^2^) [56]. Prior to each scan, participants will be overnight-fasted and not undertaken any vigorous physical activity on the morning of the scan. Scans will be performed with participants wearing light figure hugging clothing without metal zips, tags, or studs and all jewellery and other metal objects will be removed before each scan. Participants will be asked to void their bladder before each scan. All scans will be performed and analysed by the same trained technician.

Quality-assurance and quality-control measures will be performed three times per week throughout the duration of the trial and before all participant scans using a body composition phantom block containing a known bone mineral density and bone mineral content value. Tolerance for the densitometer will be established from the mean of the phantom BMD by monitoring the densitometer’s performance, using ≤1% as the acceptable tolerable limit. All DXA scans will be performed according to the Nana et al. protocol [57] which involves participants lying centrally in the scanning area with their head positioned in the Frankfort plane and with their feet placed in custom made foam blocks to maintain a constant distance of 15 cm between the feet for each scan. Similarly, participants’ hands will be placed in custom made foam blocks so that they will be in a mid-prone position with a standardized gap (3 cm) between the palms and trunk [57, 58]. These custom made blocks are made of Styrofoam and are transparent under DXA. In addition, two Velcro straps will be used to minimize movement during the scan and provide a consistent body position for subsequent scans. One strap will be secured around the ankles and the other strap around the trunk at the level of the mid forearms. The Nana et al. [57] positioning protocol has previously been shown to enhance measurement precision, and minimize the typical errors associated with technical and biological variability of DXA measurements of whole and regional body composition when compared against the traditional NHANES protocol [57, 58].

### Isometric hand-grip strength

Isometric hand-grip strength will be used as a reliable and valid surrogate measure of overall muscular strength [59, 60]. Grip-strength will be measured on both hands with a calibrated hand dynamometer (Smedley, Tokyo, Japan). All measures will be performed with the participant seated in an upright position, with the arm of the measured hand unsupported parallel to the body. Before each measure, the width of the dynamometer’s handle will be adjusted to each participant’s hand size so that the middle phalanges rest on the inner handle. Participants will then be instructed to exert maximal force. For each participant, one ‘test’ trial will be allowed before three consecutive test measurements are undertaken, alternating between each hand, with ~60-s rest intervals between each measure. The mean of the three measures from each hand will be used for the purpose of analyses. All measures will be recorded to the nearest 0.5 kg.

### Physical performance battery

The Short Physical Performance Battery (SPPB) is a well-established, reliable and valid measure of lower extremity performance [61, 62]; the SPPB evaluates lower extremity function by measuring three domains of physical function which mimic activities of daily living: 1) balance; 2) usual gait speed; 3) chair stands. For the assessment of balance, participants will be required to maintain 3 hierarchical standing postures (feet together, semi-tandem, full tandem) for up to 10 s. Usual gait speed will be assessed over a measured distance of 4-m (4-m) where participants will be asked to walk the measured distance at their usual walking speed, without acceleration. Participants will be asked to complete the 4-m walk on two separate occasions. The total time of each measure will be recorded using a stopwatch, with the mean of the two measures used for the purpose of analyses. For chair stands, participants will be instructed to perform a timed test of five repetitions of rising from a seated position and subsequently returning to their original seated position as quickly as possible, without upper extremity assistance (i.e. arms folded across their chest). The time taken to complete the 5 sit to stands will be recorded. This measure will be performed in duplicate with the mean of the two measures used for the purpose of analyses. For consistency, the same chair will be used for all assessments. Results from each of the 3 tests will be ranked using a 0–4 scale, with a value of 0 indicating inability to complete the test and 4 being the highest level of performance [63]. The composite score will be summed, with scores ranging from 0 (worst performance) to 12 (highest level of performance) [63].

### Physical activity

Physical activity in the previous week will be assessed using the long version of the self-administered International Physical Activity Questionnaire (IPAQ-L). Although originally developed for application in adults between 18 and 65 years, previous studies have supported use of the IPAQ-L for estimates of physical activity in older adults ≥65 years [64, 65]. The IPAQ-L assesses duration, frequency and intensity of activities across a range of domains including recreation/leisure, work, transportation and household/yard. Data obtained from the IPAQ-L will be used to estimate the total amount of physical activity completed in a 7-day period by weighting the reported minutes per week in each domain by a metabolic equivalent (MET) energy expenditure estimate. MET minutes per week will then be calculated by multiplying the duration (minutes), frequency (days) and MET intensity, and summing across the different domains, which include vigorous, moderate and walking, to produce an estimate of total physical activity per week (MET-min/wk.^−1^) [66]. Data on total sitting time will also be collected from the IPAQ-L with participants asked to report time spent sitting while at work, at home and leisure-time during the previous 7 days.

### Health related quality of life

Quality of life will be assessed using the self-administered short-form 36 (SF-36) health survey which covers health related quality of life across mental and physical domains. The SF-36 health survey is a 36-item questionnaire assessing eight domains of health and quality of life: physical functioning, role limitations due to physical health, pain, general health, vitality, social functioning, role limitations due to emotional problems and emotional wellbeing. Scoring of the questionnaire will be assembled using the Likert scaling method for summated ratings with raw scores transformed into 0–100 scales, with 0 and 100 assigned to the lowest and highest possible value, respectively. Higher transformed scores indicate a better perceived health status [67]. For the purpose of the present study, the Australian adaptation [68] will be used.

### Baseline questionnaires

Participants will be asked to complete an additional two questionnaires at baseline only; 1) demographic questionnaire: participants will be asked to identify age, gender, level of mobility, use (if any) of community services at home, medication and supplement use; 2) 14-item Mediterranean Diet adherence questionnaire: At baseline, an APD will complete the 14-item Mediterranean Diet adherence questionnaire in a face-to-face interview with each participant. This brief, 14-item questionnaire has previously been validated against a full-length 137-item FFQ [69] for the assessment of adherence to a Mediterranean-style diet. Each item in the questionnaire is scored as 0 or 1, yielding a maximum score of 14 (greatest adherence) [70]. Data from this questionnaire will be used to identify associations between adherence to a Mediterranean Diet and risk of sarcopenic symptomology in future cross-sectional analyses.

### Dietary protocol

All participants, independent of their group allocation, will be prescribed an energy restricted, isocaloric diet with the macronutrient distribution being 30% protein (≥1.2 g/kg), 30% carbohydrate and 40% fat. Caloric restriction will be determined from calculations of individual estimated energy requirements using gender specific predictive equations derived by Mifflin et al. [71]. Individual requirements will be calculated and then reduced by ~30% (2100–4200 kJ/day) to facilitate ~0.5–1.0 kg weight loss per week; as the intervention progresses, the prescribed caloric restriction will be adjusted in order to achieve the desired rate and amount of weight loss. Diets will be presented in the form of a checklist and established using three different energy levels (5000–6000 kJ/d; 6000–7000 kJ/d; 7000–8000 kJ/d).

As a component of the energy restricted diet, participants will be randomised to receive either: a) 375 g/d of high carotenoid vegetables, 300 g/d high carotenoid fruit, and 40-60 ml EVOO; or b) 375 g/d of lower carotenoid vegetables, 300 g/d lower carotenoid fruit, and 40-60 ml PUFA based oil. The serving size of EVOO and PUFA oil will be dependent on the prescribed energy level of the participant. Due to the versatility of EVOO, participants randomized to receive the PUFA based oil will be counselled on using any number of PUFA based oils of choice, including sunflower, rice bran, canola or peanut oils, however participants will be instructed not to consume EVOO. A list of the key prescribed fruits and vegetables (high or lower carotenoid) is presented in Table 2.

**Table 2 Tab2:** High versus lower carotenoid fruits and vegetables^a^

High Carotenoid Fruits and Vegetables^b^	Lower Carotenoid Fruits and Vegetables^c^
Fruit	Fruit
Rockmelon, watermelon, strawberries, raspberries, mango, blueberries, blackberries, red grapes, oranges, plums, pineapple, papaya, peach, nectarine, apricot, grapefruit, Avocado	Apples, pears, bananas, kiwifruit, green grapes, mandarin
Vegetables	Vegetables
Sweet potato, pumpkin, carrot, red capsicum, yellow capsicum, broccoli, kale, tomato, spinach, dark green lettuce, corn, red cabbage, beetroot, eggplant	White potato, cauliflower, green capsicum, mushroom, iceberg lettuce, peas, green beans, green cabbage, fennel, parsnip, cucumber

*Abbreviations: EVOO* Extra-virgin olive oil, *PUFA* Polyunsaturated fatty acids

^a^Depending on their allocation, participants will be asked to consume fruits and vegetables from the allocated list only

^b^Participants randomized to the high carotenoid plus EVOO group will be asked to consume 375 g/d of high carotenoid vegetables and 300 g/d high carotenoid fruit

^c^Participants randomised to the lower carotenoid plus PUFA oil group will be asked to consume 375 g/d of lower carotenoid vegetables and 300 g/d lower carotenoid fruit

All participants will receive individual dietary counselling by an APD and will be provided detailed instructions on how to maintain and record their daily dietary checklist. If any deviations are made from the prescribed quantities in the checklist, participants will be instructed to record this. All participants will be provided with a selection of recipes, reflecting the composition of the dietary protocol. In addition, all participants will be provided a list outlining the type and variety of fruits and vegetables required for consumption. If participants request mid-meal snacks between meals, they will be counselled on selecting high protein based options. Volunteers will return the checklists every fortnight and these will be discussed with the APD to clarify serving sizes and address any potential issues or problems with compliance toward the dietary protocol. As an additional measure of adherence to the dietary protocol, body weight will be recorded each fortnight for the duration of the study. All participants will be asked to maintain their habitual level of physical activity for the duration of the study. All individual consultations will last between 20 and 30 min in duration. To facilitate compliance, all participants will be provided with a sample fruit and vegetable hamper valued at $30AUD each fortnight for the duration of the study, reflecting the key fruits and vegetables specific to their group allocation. Participants randomized to the high-carotenoid fruits and vegetables, plus EVOO group will also receive EVOO for the duration of the study. All other food(s) prescribed in the energy restricted diet will be provided by the participant.

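### Only the EVOO arm is supplied with its prescribed oil, so free supply of a component worth roughly a quarter of prescribed energy is confounded with allocation

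*Protocol article*

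**What the plan says.** The Dietary protocol section of the protocol article gives both arms an isocaloric, energy-restricted diet with the same macronutrient split and the same volume of oil. One arm is allotted "375 g/d of high carotenoid vegetables, 300 g/d high carotenoid fruit, and 40-60 ml EVOO"; the other, "375 g/d of lower carotenoid vegetables, 300 g/d lower carotenoid fruit, and 40-60 ml PUFA based oil". The volume varies with the energy prescription: "The serving size of EVOO and PUFA oil will be dependent on the prescribed energy level of the participant".

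Supply is not the same. On the intervention side, "Participants randomized to the high-carotenoid fruits and vegetables, plus EVOO group will also receive EVOO for the duration of the study". The next sentence leaves the rest to the participant: "All other food(s) prescribed in the energy restricted diet will be provided by the participant". Control participants choose their oil: they "will be counselled on using any number of PUFA based oils of choice, including sunflower, rice bran, canola or peanut oils".

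The same section says that, to help compliance, every participant gets a fruit and vegetable hamper worth 30 Australian dollars each fortnight, matched to the allocated list. No reason is given for treating the oil differently, and the limitations in the Discussion do not mention it.

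**The concern.** The trial asks whether carotenoids and olive-oil polyphenols preserve muscle during weight loss. Free supply is not part of that question. The protocol uses free food to raise adherence and balances it for fruit and vegetables, but not for the oil, which is the most energy-dense item that differs between the diets.

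The possible path to bias is this. People on a weight-loss diet who must buy 40-60 ml of oil a day may use less than people who are handed it. If they do not replace the energy, their deficit is larger, they lose more weight, and some of that loss is lean tissue. The control arm would then lose more ASM for a reason unrelated to carotenoids or polyphenols, and the difference would read as preservation by the intervention. Intention-to-treat analysis keeps everyone in the comparison but does not remove a difference in how the diets were delivered.

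**Working it through.** **Inputs from the protocol article.** Oil 40-60 ml/d in both arms; energy levels 5000-6000, 6000-7000 and 7000-8000 kJ/d; a deficit of 2100-4200 kJ/d for about 0.5-1.0 kg/week; 12 weeks (Dietary protocol). About 25% of weight lost is fat-free mass, FFM (Background). Difference 0.9 kg, SD 1.2 kg, 56 participants for 80% power, 73 recruited (Power calculations).

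**Assumptions, not in the documents.** Oil density 0.92 g/ml (0.91-0.92) and 37 kJ/g (37-37.7); 40, 50 and 60 ml go with the low, middle and high energy levels; 40-50% of FFM lost is appendicular; the size of any shortfall and of its replacement by other food.

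**Step 1. The plan's own figure.** n per arm = 2 × (1.960 + 0.842)² × (1.2/0.9)² = 27.9, so 28 per arm and 56 in total. This reproduces. The standard error of the difference is 1.2 × √(2/28) = 0.32 kg.

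**Step 2. Energy in the oil.** Volume × 0.92 × 37:
- 40 ml: 1362 kJ, which is 22.7% of 6000 to 27.2% of 5000 kJ/d
- 50 ml: 1702 kJ, which is 24.3% of 7000 to 28.4% of 6000 kJ/d
- 60 ml: 2042 kJ, which is 25.5% of 8000 to 29.2% of 7000 kJ/d

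Over the assumed ranges for density and energy per gram, the share runs from 22.4% to 29.7%. If volume were not tied to energy level, the extremes would be 17% (1362/8000) and 41% (2042/5000), but the protocol says that it is tied.

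**Step 3. From a shortfall to ASM, with the protocol's own ratios.** Extra weight loss in kg = (kJ/d not eaten / 2100) × 0.5 × 12. FFM = 0.25 × that. ASM = 0.40 to 0.50 × FFM.

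Worked case, half of 50 ml not used and not replaced: 851/2100 × 0.5 × 12 = 2.43 kg of weight; × 0.25 = 0.61 kg of FFM; × 0.40-0.50 = 0.24-0.30 kg of ASM.

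| Control shortfall | Energy replaced | ASM, 40 ml (kg) | ASM, 50 ml (kg) | ASM, 60 ml (kg) |
|---|---|---|---|---|
| a quarter | none | 0.10-0.12 | 0.12-0.15 | 0.15-0.18 |
| half | half | 0.10-0.12 | 0.12-0.15 | 0.15-0.18 |
| half | none | 0.19-0.24 | 0.24-0.30 | 0.29-0.36 |
| all | none | 0.39-0.49 | 0.49-0.61 | 0.58-0.73 |

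**Step 4. Scale.** Half-use with no replacement, 0.19-0.36 kg, is 22-41% of 0.9 kg and 0.6-1.1 standard errors. With a true effect of zero, the two-sided 5% test would reject in about 9-21% of trials (normal approximation). With half the energy replaced at 50 ml, 0.12-0.15 kg is 13-17% of 0.9 kg and under half a standard error, and the rejection rate is about 7-8%.

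**Step 5. Would the planned checks notice?** Half-use adds 681/2100 × 0.5 = 0.16 kg/week at 40 ml and 1021/2100 × 0.5 = 0.24 kg/week at 60 ml. That can fit inside the intended 0.5-1.0 kg/week, so it need not prompt any adjustment of the restriction.

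**The case against.** The strongest reply is that the harm depends on a behaviour the documents do not show. Nothing in the protocol says that controls will use less oil because they buy it. The product is ordinary cooking oil, and free choice among several types may make it easier to comply. That is correct: low uptake is plausible, not established.

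The protocol also has checks that apply to both arms. Participants keep a daily checklist with prescribed quantities and record deviations. A dietitian reviews it each fortnight and takes up compliance problems. Weight is taken each fortnight, and the restriction is adjusted toward the desired rate of loss. These would dampen the effect but not remove it. The checklist is self-reported, and the Discussion says there is no blood or urine marker. A control who skips oil loses more weight, so weight alone would look like good adherence.

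The direction is not certain either. The 25% FFM share is an average for energy restriction, while this diet is high in protein and leaving out oil removes none of it. Participants who want snacks are steered to high-protein options, so a control who replaces oil in that way might protect lean mass.

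A reader might infer that the arms are prescribed different energy. They are not: volume, energy and macronutrients match, and only the supply of the oil differs. The wording "participants randomized to receive the PUFA based oil will be counselled on using any number of PUFA based oils of choice" might also suggest that controls are given oil, but the sentence leaving all other food to the participant rules that out in this article.

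**Conclusion.** The point holds as a design weakness. An adherence aid that the protocol balances for fruit and vegetables is given to one arm only for a component worth about 22-30% of prescribed energy, and nothing in the article offsets it. The share rests on the assumed oil density, energy per gram and pairing of volume with energy level.

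The ASM figures are illustrations, not predictions. About 0.2-0.4 kg requires that every control leaves out half the oil for all 84 days, replaces none of it and draws no response from the dietitian. About 0.12-0.15 kg follows at 50 ml if half that energy is replaced. Both also rest on the 25% FFM share and on 40-50% of it being appendicular.

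A reader might go further and conclude that the unequal supply will produce a false benefit, or could account for the whole 0.9 kg. The documents support neither. No shortfall is shown, and even complete omission with no replacement reaches only about 0.4-0.7 kg on these ratios. A reader might also expect more drop-out among controls, but the documents give nothing from which to size that. What is supported is narrower: a positive ASM result would be harder to attribute to carotenoids and polyphenols, and the weakness is cheap to avoid.

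**What to change.** Supply control participants with a PUFA-based oil of their choice, from the types already listed, in the volume already prescribed, at the existing fortnightly visits. This changes no prescription and keeps the comparator as the protocol defines it.

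The cost is material. 40 ml × 84 days = 3.4 L and 60 ml × 84 days = 5.0 L of cooking oil per control, for about 36 controls (half of 73), handed out at 0.56-0.84 L per fortnight. No new visit or measurement is needed.

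If supply can no longer be changed, summarise checklist-recorded oil intake and weight change by arm beside the ASM result, and name the unequal supply as a limitation. This uses data already collected. It makes the problem visible but does not remove it, because the intake record is self-reported.

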### Power calculations, intention to treat and statistical analyses

This study was powered on the primary outcome of change in ASM. Based on data from a previous intervention assessing preservation of ASM during intentional weight loss in obese older adults [22] it was estimated that *n* = 56 participants would provide 80% power to detect a significant (*P* < 0.05, 2-sided) change in ASM between the two study groups of 0.9 kg ± 1.2 kg. Assuming an attrition rate of 30%, the target sample size will be *n* = 73 participants. All analyses in the proposed study will be performed using intention-to-treat analysis, with all randomised participants included in the final analysis irrespective of compliance.

Non–normally distributed variables will be logarithmically transformed before analysis. Where normality is not achieved, non-parametric methods for analyses will be used. Descriptive statistics will be presented for baseline characteristics, and independent sample t-tests or chi square analysis will be used to ensure that there are no significant differences between randomised groups. Paired t-tests will be used to identify whether outcome parameters change over time. After screening for assumptions related to multicollinearity, normality, linearity, homogeneity and reliability of covariates, analysis of covariance (ANCOVA) will be applied to identify differences between groups over time, with diet groups as the independent variable and outcome parameters as the dependent variable. Covariates will be determined using a correlation matrix to identify significant interactions between potential confounders. Analyses will be performed using SPSS for Windows 24.0 software (SPSS Inc., Chicago, IL, USA) with statistical significance set at *P* < 0.05.

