**Methods:**

This randomised controlled clinical trial will recruit community-dwelling, healthy overweight and obese older adults (≥60 years) for a 12-week weight loss intervention. Seventy-three participants will be recruited and randomized to an energy restricted (~30% restriction), isocaloric diet (30% protein; 30% carbohydrate; 40% fat) enriched with either: a) 375 g/d of high carotenoid vegetables, 300 g/d high carotenoid fruit, and 40-60 ml extra-virgin olive oil (EVOO); or b) 375 g/d of lower carotenoid vegetables, 300 g/d lower carotenoid fruit, and 40-60 ml Polyunsaturated fatty acid (PUFA) based oil. All participants will receive individual dietary counselling each fortnight for the duration of the study and will be asked to maintain their habitual level of physical activity throughout the study. The primary outcome will be appendicular skeletal muscle (ASM) assessed by dual energy X-ray absorptiometry (DXA). Secondary outcomes will include body weight, fat-free mass (FFM), fat mass (FM), muscle strength (Isometric hand-grip strength), physical performance (Short Physical Performance Battery), physical activity (International Physical Activity Questionnaire) and health related quality of life (SF-36). Outcomes will be measured at baseline and at week 12.

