Eligible participants will be provided with detailed study information and consent form via post or email, and scheduled to attend a baseline appointment upon providing study consent. At the baseline appointment, body mass, height and BMI will be measured to confirm eligibility. Participants will be recruited via rolling recruitment and randomly allocated to a 12-week prescribed and individualized energy restricted diet enriched with high carotenoid fruits and vegetables and EVOO; or, a 12-week prescribed and individualized energy restricted diet enriched with lower carotenoid fruits and vegetables and a polyunsaturated fatty acid (PUFA) based oil. Volunteers will be randomly assigned to either group following the completion of all baseline measurements. Allocation will be stratified by BMI (27–29.9 kg/m^2^; ≥30 kg/m^2^) using a random number, computer generated randomisation schedule generated and managed by a member of the research team. An overview of the recruitment method and randomisation process is provided in Fig. 1.

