### Data collection

The timeframe for this study will be 18 months, from 1 July 2016 to 30 April 2018. This timeframe includes the collection of all outcome measures and statistical analysis pertaining to this study**.** Assessment of all outcome measures (primary or secondary) will be conducted at baseline and Week 12. The primary outcome measure for this study will be ASM. Secondary outcomes will include body weight, FFM, FM, muscle strength, physical performance, physical activity and health related quality of life. Participants will also report to the clinic each fortnight for the duration of the study where they will be weighed and receive individual dietary counselling by an Accredited Practising Dietitian (APD).

In preparation for all outcome assessments, participants will present to the clinic after an overnight fast wearing light figure hugging clothing without metal zips, tags, or studs. Following the completion of all baseline assessments, participants will be provided with a 3-day food diary and commence a one-week ‘run-in’ period before beginning the 12-week intervention. During the ‘run-in’ week, participants will be instructed to consume their habitual dietary intake. Throughout this period, participants will be asked to record all food and fluid intake across three days (two consecutive weekdays and one weekend day). Upon completion of the ‘run-in’ week, participants will return to the weight management clinic (Week 0) where food diaries will be verbally cross-checked for completeness by an APD, and any ambiguities will be clarified. Participants will be re-weighed following completion of the ‘run-in’ week.

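### The target of 73 does not allow for 30% attrition: about 51 would be evaluable rather than 56, and power would be about 75–76% rather than 80%

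*Protocol article*

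**What the plan says.** The section on power calculations, intention to treat and statistical analyses bases the sample size on the primary outcome, change in appendicular skeletal muscle (ASM). It states that "56 participants would provide 80% power to detect" a "change in ASM between the two study groups of 0.9 kg ± 1.2 kg", at a two-sided 5% level. It continues "Assuming an attrition rate of 30%, the target sample size will be" 73. The Methods part of the abstract repeats the target: "Seventy-three participants will be recruited and randomized". The article gives no other attrition figure and no other reason for 73.

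Two further statements bear on what attrition costs. Under Data collection: "Assessment of all outcome measures (primary or secondary) will be conducted at baseline and Week 12". The power section also says that the analysis is by intention to treat and keeps all randomised participants whatever their compliance.

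**The concern.** Three figures are stated together: 56 participants for 80% power, 30% attrition, and 73 to be randomised. They cannot all hold. Adding 30% to 56 gives 73, but taking 30% away from 73 does not return 56, because the loss applies to the larger number.

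What is at stake is the declared power for the primary question. If ASM shows no significant difference, a reader will judge that result against a planned power of 80%. On the plan's own attrition assumption, that power would not have been available.

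**Working it through.** **Inputs from the article.** Difference in ASM change 0.9 kg; variability 1.2 kg; two-sided alpha 0.05; power 80%; 56 participants; attrition 30%; target 73.

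**Assumptions.** The ± 1.2 kg is read as the SD of change, and allocation is taken as 1:1, since the ratio is not stated. Together these reproduce the plan's 56.

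**Step 1: reproduce 56.** By the normal approximation, n per group = 2 × (1.96 + 0.8416)² × (1.2/0.9)² = 27.9, so 28 per group and 56 in total. Power at 28 per group is 80.1%. A two-sample t-test needs 28.9, so 29 per group (58 in total), and gives 78.7% at 56. The plan's figure is therefore the normal-approximation one.

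**Step 2: reproduce 73.**
- Multiplying: 56 × 1.30 = 72.8, rounded up to 73. This matches the plan.
- Dividing: 56 / (1 − 0.30) = 80. This does not match.

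**Step 3: evaluable participants at 30% attrition.** 73 × 0.70 = 51.1, so about 51, split 26 and 25. The attrition at which 73 still leaves 56 is 1 − 56/73 = 23.3%.

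**Step 4: power with 51.** The standard error of the difference is 1.2 × √(1/26 + 1/25) = 0.336 kg. By the normal approximation, 0.9/0.336 − 1.96 ≈ 0.72, which corresponds to a power of 76.3%. The t-test figure comes from the noncentral t distribution.

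| | 56 evaluable | 51 evaluable | Change |
|---|---|---|---|
| Power, normal approximation | 80.1% | 76.3% | −3.8 points |
| Power, t-test | 78.7% | 74.7% | −4.0 points |
| Type II error, normal approximation | 19.9% | 23.7% | × 1.19 |
| Type II error, t-test | 21.3% | 25.3% | × 1.19 |
| Difference detectable with 80% power, normal approximation | 0.90 kg | 0.94 kg | about +0.04 kg |
| Difference detectable with 80% power, t-test | 0.915 kg | 0.96 kg | about +0.045 kg |

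**Step 5: what 30% attrition would require.** To keep 56 evaluable: 56/0.70 = 80 randomised. To have 80% power by t-test: 58/0.70 = 82.9, so 83 randomised.

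**The case against.** **Intention to treat keeps all 73.** The article includes everyone randomised irrespective of compliance. That deals with people who do not follow the diet, not with people who have no follow-up scan. Outcomes are measured only at baseline and week 12, so someone lost before week 12 has no follow-up ASM. The plan's own allowance for attrition accepts that dropouts cost information. This objection does not stand.

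**ANCOVA will recover the loss.** It might. If a covariate correlated at about 0.3 with ASM change, the residual variance would be multiplied by 1 − 0.3² = 0.91, about the same as 51/56 = 0.91, and the shortfall would be offset. But 0.3 is an assumption, and the stated calculation takes no credit for covariates. The point makes the problem less serious; it does not make the stated figure right.

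**The shortfall is small.** This stands. The gap to the correct target is 7 participants and about 4 points of power. No estimate is biased, and 73 still delivers 56 evaluable if attrition stays at or below 23%.

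**A larger effect might be inferred.** Setting the t-test power at 51 (74.7%) against the nominal 80% suggests a loss of about 5 points and a type II error one quarter larger. That mixes two methods: about 1.3 points of the gap come from t-test versus normal approximation at 56, not from the attrition step. Comparing 0.96 kg with 0.90 kg has the same fault.

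**The effect size might also be questioned.** The Discussion says that the cited trial combined its supplement with resistance training, and a reader might infer that 0.9 kg does not carry over to this diet-only trial. The article does not show how 0.9 kg was derived from that trial or whether its comparator group also trained. The inference would need the cited source and forms no part of this point.

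**Conclusion.** The sample size sentence is wrong as written. The figure of 73 matches multiplication by 1.30, whereas the stated 30% attrition calls for division by 0.70. On the plan's own assumptions about 51 participants would be evaluable. Power for 0.9 kg would be about 76% on the plan's apparent method, or about 75% by t-test: about 4 points lost on either method, with a type II error about one fifth larger.

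The size of the loss rests on 1:1 allocation, on 1.2 kg being the SD of change, and on no credit for covariate adjustment. The mismatch between 56, 30% and 73 needs none of these.

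A reader might go further and conclude that the trial must enrol more people. The documents do not support that. What they show is a power statement that does not match its attrition rate, and that can be corrected by stating the power or the attrition allowance accurately.

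**What to change.** In the power section, replace the attrition sentence with one of these:

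- 73 randomised with 30% attrition leaves about 51 evaluable, giving about 75–76% power for 0.9 kg (SD 1.2 kg). Say whether the figure comes from the normal approximation (76%) or the t-test (75%).
- 73 randomised allows for at most 23% attrition if 56 are to be evaluable.

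Either is a change to one sentence. No participants are added, and the abstract can stay as it is, because it gives the 73 without any power or attrition figure. The only cost is a slightly less favourable stated power or a smaller attrition allowance.

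For reference only: keeping 56 evaluable at 30% attrition needs 80 randomised, or 83 if 80% power is required by t-test. Either would also change the number in the abstract and add 7 or 10 participants.
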